## Abstract

Innovative strategies are needed to adequately assess and monitor disease activity of patients with rheumatoid arthritis (RA) in times of scarce appointments. The aim of the TELERA study is to evaluate the feasibility and performance of asynchronous telemedicine visits based on patient-generated data and patient's drug history. RA patients use a medical app, ABATON, that captures the results of a self-performed quick CRP-test, joint-count, and electronic patient-reported outcomes in between visits. This is a prospective, multi-center, randomized controlled trial performed in four German university centers. The estimated sample size is 120 patients. The main outcome is the agreement of rheumatologists' treatment decisions based on asynchronous telemedicine patient-generated data with traditional in-person rheumatology clinic-based decisions and with patient suggestions. The TELERA trial will provide evidence regarding the implementation of remote care in rheumatology.

**Clinical Trial Registration:** This clinical trial was registered at German Registry for Clinical Trials (DRKS). http://www.drks.de/DRKS00016350, identifier: DRKS00024928.

## Introduction

The treat-to-target concept has been established as a treatment principle for rheumatoid arthritis (RA) (1). The aim of this strategy is to define a treatment target at therapy initiation and to closely monitor treatment response in order to identify insufficient treatment success and modify the therapeutic strategy as needed. This approach represents a challenge for rheumatologists as frequent, one to three-monthly assessments are recommended in patients with active disease and resources are limited (1–3). In reality, therapies are not assessed frequently enough and, therefore, are all too often not adjusted to the current state of the disease (4). At least two important reasons for the currently poor disease management are (A) the limited access to rheumatology specialists and (B) an increasing follow-up appointment deficit for already diagnosed patients. This situation is likely to worsen as the current shortage of rheumatologists in Germany and other nations will probably increase even further in the future (5, 6).

Digitalization promises new ways to improve patient care and shape a more efficient and transparent health care environment (7, 8) and the large majority of German patients with rheumatic and musculoskeletal diseases (RMD) regularly uses a smartphone (9). Electronic patient reported outcomes (ePROs) and wearables facilitate continuous digital patient monitoring (“tight control”) (9, 10). By using telemedicine, patient care could be individually adapted according to disease activity and follow-up preferences (“virtual treat-to-target”) (11). By actively involving the patient in disease monitoring, self-efficacy and activation (“patient empowerment”) can be increased (12) and ultimately remission reached earlier (13). Furthermore, the use of telemedicine could enable the rheumatologist to work more flexibly and efficiently.

The aim of this study is to evaluate the feasibility and performance of asynchronous telemedicine visits based solely on patient-generated data in RA patients.

## Methods

### General Study Design

This is a prospective, multi-center, randomized controlled trial. This study has received ethical approval by the Ethical Committee of the University Clinic of Tuebingen (# 4442020). We aim to include 120 patients with RA and written informed consent, treated at the rheumatology outpatient units of the university hospitals Duesseldorf, Erlangen, Hamburg and Tuebingen (Germany).

The overall study design is summarized in Figure 1. Prior to a regular face-to-face appointment (T0), patients with RA will be supported to carry out a structured self-examination of joints by a video and instructions from the study personnel and to perform a quick self C-reactive protein (CRP)-test. The patients will then enter the results in a study app. Furthermore, patients will be asked to answer ePROs on a weekly basis in between the regular next face-to-face appointment 3 months later (T1), when the self-examination will be repeated.

**Figure 1 F1:**
[figure not shown]
Trial flow chart. CRP, c-reactive protein; ePRO, electronic patient reported outcomes; RAPID-3, routine assessment of patient index data 3.

At each self-examination, the patient also enters his/her therapeutic suggestion: (A) escalation of therapy; (B) no therapeutic change needed; and (C) de-escalation of therapy. Based on patient history, the patient-generated data from T0, T1 and in-between visits, two independent randomized rheumatologists from other university centers will be asked to enter their therapeutic suggestion solely based on the digital information. The patient and tele-rheumatologists' suggestions are then compared to the gold standard which is the traditional therapeutic decision based on the face-to-face visit for T0 and T1.

After T1, patients complete an evaluation questionnaire and semi-structured telephone interviews will be conducted with 10 patients with RA and the four main study investigators to capture qualitative feedback concerning patient acceptance, app compliance, changes in self-management and self-efficacy.

### Study Visit

Prior to the routine clinical visits, patients are instructed to carry out a structured self-examination. This includes a self-assessed joint count, capillary-based CRP self-sampling, completion of ePROs and data entry into the study app. The duration of the study visit will be ~1 h.

**Figure 2 F2:**
[figure not shown]
Instructions for self-examination of proximal interphalangeal joints (PIP), extracted from self-examination video.

### CRP Self-Sampling

Patients receive written instructions on how to perform a semi-quantitative capillary-based CRP-test (CRP-CHECK-1,VEDALAB, Alencon, France). Any questions will be answered by the local study team, if needed, however the test should be carried out independently by patients and study personnel will only intervene to prevent harm to patients. The immunochromatographic rapid test allows semi-quantitative detection of CRP with three possible outcomes: (A) negative; <5 mg/L; (B) borderline; 5 to 10 mg/L or (C) positive; >10 mg/L. The test is currently only licensed for professional use, however we hypothesized that the test could also be carried out successfully by patients after appropriate education. Figure 3 displays an example of a negative CRP test. Supplementary Figure 1 shows the translated and adapted manual and Supplementary Figure 2 the interpretation guide.

**Figure 3 F3:**
[figure not shown]
Example of a negative CRP test (T-line is more intense in color than C-line).

### Study App and ePROs

The ABATON web-app is a medical device developed and maintained by ABATON GmbH (Berlin, Germany). This app provides a study module which has been adopted to this trial. All digital administered questionnaires, forms and monitoring instruments were pre-configured. Each study center has access to the web-based study module via their own study account. Patients get invited by the respective clinical site study personnel via a short messaging system (SMS) invite which contains the personalized link for the patient. All questionnaires were administered on the patient's own phone (“bring your own device”). In addition to questionnaires completed by patients, all study relevant documentation (for example therapeutic suggestions of tele-rheumatologists) is performed digitally by the study personnel and patients. In addition to forms and questionnaires listed in Table 1, ABATON provides documentation for other parameters (Lab CRP, tender- and swollen joint count (TJC/SJC), medication information) and allows to add extra notes. In between visits, the patients are being asked to complete the RAPID-3 (routine assessment of patient index data 3) questionnaire and to state if they experienced a disease flare. If the flare question is answered with yes (“Did you experience a flare of your disease in the past 7 days?”), the patients are being asked to specify the duration (1–7 days) on a numeric rating scale with anchors (“On how many days did you experience the disease flare (in days)”). A reminder logic is implemented to remind the patients 3 consecutive days if they have not filled out the questionnaires and stop as soon as the due questionnaire is completed. Results are immediately available to the patient and the study site via the web-based dashboard. A graphical dashboard for the frequently entered questionnaires/scores is available to the patient all the time (see Figure 4). After having completed the T1 visit, patients will receive questionnaires to evaluate the app and the study experience via the study app after being manually triggered by the study personnel.

**Table 1 T1:** Overview of questionnaires and data entered into ABATON software by patients, local rheumatologists and tele-rheumatologists.

**Name**	**Assessment**	**Filled by**	**Frequency**	**No. questions**
RAPID-3	Physical function, pain and global health	Patient	Weekly	15
Flare question	flares	Patient	Weekly	1–2 (two if patient experienced flare)
Auto-DAS-28 (CRP)	Disease activity	Patient	T0 and T1	5
PAM-13	Patient activation	Patient	T0 and T1	13
TELERA-set		Patient	T0 and T1	5
System-usability-scale	Usability and acceptance of ABATON app	Patient	T1	10
Net-Promoter-Score	Willingness of patients to recommend ABATON app	Patient	T1	1
Medical history	Disease duration, current and prior treatments, CRP-value.	Local rheumatologist	T0	3
Treatment question	Treatment decision (escalation, de-escalation or no change)	Local rheumatologist, Tele-rheumatologist 1, Tele-rheumatologist 2	T0 and T1	3

*CRP, c-reactive protein; PAM-13, patient activation measure 13; RAPID-3, 3 routine assessment of patient index data-3*.

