### Primary and Secondary Outcomes

Primary outcome will be the agreement of therapeutic suggestions of patients and tele-rheumatologists compared to the gold-standard, the therapeutic decision by the local rheumatologist.

Secondary endpoints will include: the overall usability and acceptance of the study app [measured by the System-Usability Scale by patients and physicians (SUS) and Net-Promoter Score (NPS)]; the agreement of patient- vs. physician-performed joint count; agreement of venous and capillary based CRP; willingness to perform CRP quick test among patients (NPS); travel time to rheumatologist (hours); agreement of tele-rheumatologist and local rheumatologist-based clinical disease activity index (CDAI); agreement of patient-based disease activity score (Auto-DAS28-CRP) and local rheumatologist-based DAS-28 CRP; change in patient's confidence for self-management (Patient Activation Measure, PAM) over time; willingness to substitute routine appointments for telemedicine appointments among patients (NPS); change of perceived assessment accuracy of rheumatologists and patients concerning patient disease activity since the last appointment (VAS 0-10).

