## Discussion

TELERA is an exploratory study to assess the feasibility and performance of asynchronous telemedical assessments of patients with RA. The overall aim is to move current rheumatology care toward a needs-based approach with the help of remote care. Currently, the number of new rheumatologists is declining (3) and it still takes multiple months for patients to see a rheumatologist (25). However, we could demonstrate that the majority of patients and rheumatologists agreed that patients in remission do not need to be seen in person (26). The recently published EULAR guidelines highlight the importance of self-management skills and potential of mobile apps to improve the clinical care of people with RA (27). Importantly, Thurah et al. could previously demonstrate in a RCT that a remote care approach was safe and not inferior to conventional management in RA (28). In this RCT, 294 patients with RA were requested to complete ePROs and a CRP measurement each 3–4 months. The CRP measurement was however not performed by patients themselves, no joint-count was carried out and ePRO questionnaires were completed before tele-health follow-ups, which were synchronous. Based on our previous work (9), we chose a 1 week ePRO frequency, providing rheumatologists and patients with continuous disease activity data and including self-sampling (26, 29). Furthermore, we wanted to see if our study confirms previous results showing a significant increase in patient activation (PAM) after using an RA monitoring app (12). The benefits of an intensive RA telemonitoring strategy have also been demonstrated by Salaffi et al. (13), who could show that patients with early arthritis reach the state of remission more often and faster when receiving frequent telemonitoring and treatment adjustments according to a standardized treatment protocol rather than standard of care. In our opinion, the simple shift from physical in-person visits to virtual visits will not result in a significant liberation of resources and in particular time of rheumatologists. Nevertheless, asynchronous visits give patients and rheumatologists the freedom of time and place. By using a combination of objective and subjective markers for disease-activity self-assessment, patients can inform their rheumatologists in detail about their health status. Based on this remote patient-generated information, rheumatologists should continuously adapt the follow-up strategy incorporating remote care strategies (30): in case a patient achieves remission after therapy induction, the subsequent ePRO frequency could be extended and a remote follow-up (i.e., telephone call) after 3 months could be scheduled instead of a face-to-face meeting. Web based asynchronous home telemonitoring is already an integral part in the care of other chronic diseases such as diabetes and heart disease (31), as well as inflammatory bowel disease (32) and has great potential in rheumatology (33). To the best of our knowledge, this is the first trial evaluating the potential of asynchronous telemedicine visits based on patient-based joint counts, self-performed CRP and ePROS in RA patients. Furthermore, it is the first study comparing treatment decisions of patients, rheumatologists and tele-rheumatologists. A major strength of this study is the early patient involvement. The study design and protocol was designed in close cooperation with three official patient research partners of the German League against Rheumatism (Deutsche Rheuma-Liga Bundesverband e.V.) who commented on and edited the draft version and approved the final study protocol. We deliberately chose a risk-adverse study setting, where participation has only a minimal impact on clinical care (rheumatologists have access to ePROS in-between visits). This study design has some limitations. Patients eligible for the study need to be in possession of a smartphone and need to have a sufficient level of understanding and dexterity to use the app, resulting in exclusion of some elderly or cognitively impaired, as well as underprivileged patients without smartphone or network access. This is a general limitation in app-based remote health care monitoring and will most probably change within the next decades. Similary, the chose time-frame limits the analysis to two appointments per patient.

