
Due to the exploratory study character, patients will not be stratified by disease duration, activity or previous treatments. Analyses will however be adjusted for these possible confounders. Furthermore subgroup analyses will be performed to assess potential differences between patients in remission or with active disease. Also, remote evaluation can be difficult in patients with recent treatment changes who have experienced some improvement but still have active disease. For these cases, remote rheumatologists receive information on previous therapies including recent changes.

The usage of semi-quantitative CRP tests provides only a certain degree of accuracy. However, this is a simple testing system that could be performed at home without the need of extensive equipment. Further, after discussing the options with patients, it seemed more important to receive approximate results in a short period of time than exact results after multiple days.

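### Independence of the two sides of the primary agreement comparison is not secured, so agreement is liable to be inflated

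*Protocol article*

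**What the plan says.** Primary and Secondary Outcomes defines the primary outcome as "the agreement of therapeutic suggestions of patients and tele-rheumatologists compared to the gold-standard, the therapeutic decision by the local rheumatologist". General Study Design (text after Figure 1) describes that reference as "the traditional therapeutic decision based on the face-to-face visit for T0 and T1".

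**Reference side.** Under General Study Design and Study Visit, the patient does the self-examination before the clinic visit. The patient's own choice of escalation, no change or de-escalation is entered at the same time. Study App and ePROs then states: "Results are immediately available to the patient and the study site via the web-based dashboard". The Discussion, explaining a deliberately cautious setting, says that "rheumatologists have access to ePROS in-between visits". Data Collection and Web-Based Study Module has the local and tele decisions entered through the same application.

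**Tele side.** The Introduction states the aim as "asynchronous telemedicine visits based solely on patient-generated data in RA patients". General Study Design bases the tele decisions on more: "Based on patient history, the patient-generated data from T0, T1 and in-between visits". In Table 1 the medical history completed by the local rheumatologist at T0 comprises "Disease duration, current and prior treatments, CRP-value". Study App and ePROs adds that the platform can also hold laboratory CRP, joint counts, medication and free notes. The Discussion says that "remote rheumatologists receive information on previous therapies including recent changes".

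**The concern.** An agreement study tells us something only if each side reaches its decision without the other side's information. Here the reference rater has access to the app data on which the tele decision rests, and possibly to the patient's own suggestion, before recording the decision that counts as truth. In the other direction, a clinic-entered CRP value, and possibly other clinic entries, may reach the tele rater. It could then stand in for the self-test whose adequacy the study examines.

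Shared information of this kind generally raises agreement. The trial's main message would be that remote decisions reproduce clinic decisions. A high kappa cannot support that message if the two sides may have worked from the same material. More patients would not remove the problem, and exposure that is not recorded during the trial may be impossible to reconstruct later.

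**Working it through.** **1. The plan's own figure.** Sample Size gives 96 analysed patients after 20% dropout: 120 × (1 − 0.20) = 96. This reproduces and is not in dispute. The article states no expected kappa, decision frequencies or precision, so no figure for the primary outcome can be reproduced.

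**2. What the reference rater can see, by visit.**
- T0: that day's self-examination and the patient's suggestion, both entered before the visit. There are no weekly ePROs yet.
- T1: the same items, plus about 12 weekly questionnaires collected over the three months since T0.
- The article states access. It states neither that the local rheumatologist looks at the entries before deciding, nor any rule that delays access until the decision is saved.

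**3. What the tele rater can see.**
- The Introduction allows only patient-generated data, the Abstract adds drug history, and Table 1 adds a locally entered CRP value to the T0 history. The CRP value fits neither description.
- General Study Design lists T0, T1 and in-between data together and gives no cut-off for the T0 decision.

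**4. How much shared information could matter (illustration).** Assumptions:
- k0 is the kappa that independent decisions would give.
- s is the share of reference decisions made to coincide with the comparator through shared information.
- Both raters have the same category frequencies, and these do not change.

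With po and pe the observed and chance agreement:
- po′ = (1 − s)·po + s
- kappa′ = (po′ − pe)/(1 − pe) = (1 − s)·k0 + s = k0 + s(1 − k0)

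Worked case with assumed frequencies 0.20/0.70/0.10 and k0 = 0.40:
- pe = 0.04 + 0.49 + 0.01 = 0.54
- po = 0.54 + 0.40 × 0.46 = 0.724
- at s = 0.2, po′ = 0.8 × 0.724 + 0.2 = 0.779 and kappa′ = (0.779 − 0.54)/0.46 = 0.52

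| k0 | s = 0.1 | s = 0.2 | s = 0.3 |
|---|---|---|---|
| 0.30 | 0.37 | 0.44 | 0.51 |
| 0.40 | 0.46 | 0.52 | 0.58 |
| 0.60 | 0.64 | 0.68 | 0.72 |

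The rise runs from 0.1 × 0.4 = 0.04 to 0.3 × 0.7 = 0.21. For a given s it is an upper bound, because the model lets every influenced decision agree with the comparator.

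**5. Comparison with sampling error.** The approximate 95% half-width is 1.96·√[po(1 − po)/(n(1 − pe)²)]. With n = 96, one rating pair per patient and s = 0, it is 0.15 to 0.29 over assumed frequencies 0.20/0.70/0.10, 0.30/0.60/0.10 and 0.10/0.85/0.05 and the three values of k0. The upper part of the possible bias is therefore of the same order as the random error, but unlike random error it does not shrink with n.

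**The case against.** The strongest reply is that access is not use. The reference is defined by the face-to-face visit, and Routine Clinical Assessment gives that visit its own inputs: physician joint count, venous CRP and physician global assessment. View rights and data locks are details that an article may leave to the full protocol. The trial is declared exploratory, and the ePRO access is disclosed as a deliberate, cautious choice. Much of this stands, and it rules out several stronger readings:

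- A reader might infer that the local decision is made with the app data in view, or that agreement is inflated as a matter of fact. The text shows availability, not viewing, and inflation is likely but not demonstrated.
- A reader might infer that the T0 tele decision uses T1 data. That is only one reading of General Study Design. The sentence may equally mean each visit's own data. Hindsight could also move T0 agreement in either direction.
- A reader might see a conflict between Table 1, which schedules treatment history at T0 only, and the Discussion, which promises recent changes to the remote raters. There is none. Study App and ePROs says the platform documents medication in addition to the Table 1 forms, and Data Collection has local staff add current medication. A T1 rater also needs to know current therapy in order to judge escalation.
- The Abstract's mention of drug history answers most of the mismatch with the Introduction. The CRP value remains, and Table 1 does not say whether it comes from the same visit.
- The kappa illustration applies to one comparison at a time. A local decision that follows the patient's suggestion raises patient–local agreement, but not necessarily tele–local agreement.

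What the reply does not remove is the stated access, the order of entry before the visit, and the fact that the Discussion never weighs that access against the agreement endpoint.

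**Conclusion.** The point holds as a weakness in how the primary comparison is secured. As written, the plan lets the reference draw on the data it judges, and it does not clearly keep clinic-derived information or later data from the tele raters. Agreement is therefore liable to be too high, and the T1 reference is the more exposed because it follows three months of weekly ePRO access.

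The size of any bias cannot be derived from the article. Under the assumptions shown, kappa would rise by at most s(1 − k0), or 0.04 to 0.21 for k0 of 0.30 to 0.60 and s of 0.1 to 0.3. Both quantities are assumed, as are the category frequencies behind the half-widths. The text does not support a claim that contamination has occurred. It also does not support abandoning T1 as part of the primary outcome: T1 is the only visit informed by between-visit monitoring, and enrolment has already begun.

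**What to change.** 1. **Order of entry at the site.** Have the local decision saved in ABATON before that visit's patient suggestion and self-examination results open to the local rheumatologist. Keep the between-visit ePRO access described in the Discussion, and reconcile the ordering explicitly with the cautious rationale given there.
2. **Tele view.** Limit each tele decision to data up to that visit, with the medication as it stood before the visit. Hide same-visit venous CRP, physician joint counts, notes and the local decision until the tele decision is locked. State what the CRP value in Table 1 is, and bring the Introduction, the Abstract and Table 1 into line.
3. **Reporting.** Keep both visits in the primary outcome, but report T0 and T1 agreement separately and note that the T1 reference followed weekly ePRO access.
4. **Visits already done.** Use platform time stamps if they exist, or record whether app data were seen before the decision. Run a sensitivity analysis that excludes exposed decisions.

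The cost is a change to access rights and a short amendment. Each per-visit estimate would rest on up to 120 patient-visits instead of 240 and be less precise. One limit remains: patients can voice their preference in the consultation, so patient–local agreement cannot be made fully independent, and the report should say so.
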